#### **VIII. Quality of life (EQ-5D-5L)**

Overall health can be assessed with the EQ-5D-5L [37]. The EQ-5D-5L is a generic health-related instrument frequently used in clinical environments to measure quality of life. It comprises 5 questions/dimensions (mobility, self-care, usual activities, pain, depression) with Likert-scale response and a visual analogue scale where patients are asked to rate their overall health from 0 (the worst health imaginable) to 100 (the best health imaginable). Each dimension allows to choose five levels labelled as (1) 'not /no problems', (2) 'slight problems', (3) 'moderate problems', (4) 'severe problems', and (5) 'unable to' (mobility, self-care, usual activities), 'extreme' (pain/depression), or 'extremely' (anxiety/depression). Using the EQ-5D-5L, a total of 3125 different health states can be described. The final EQ index is a number between 0 and 1, with 0 indicating the poorest possible health (a state as bad as being dead) and 1 indicating the best possible health.

#### **IX. Swiss spinal stenosis questionnaire**

The Swiss Spinal Stenosis Questionnaire is a self-report outcome questionnaire for patients with LSS that is often used in clinical studies to assess treatment outcomes in this disease. The Swiss Spinal Stenosis Questionnaire assesses the intensity of symptoms, physical function, and patient satisfaction following treatment [38].

#### **X. Tampa scale of kinesiophobia**

The Tampa scale is a 17-item self-report questionnaire based on the assessment of fear of exercise, fear of physical activity, and fear avoidance. It consists of two subscales. While activity avoidance revolves around the reflection of activities that may increase pain or cause injury somatic focus investigates the reflection of beliefs and underlying serious conditions [39, 40].

#### **XI. Core Outcome Measures Index for the back (COMI back)**

The COMI is a validated 11-item self-report questionnaire. It is used routinely worldwide for assessing the main outcomes of importance to patients back problems. However, it might be expected to be less responsive than a disease specific questionnaire [41].

#### **XII. Upper body motion (inertial sensor data)**

During all tasks, inertial sensor data will be collected. Inertial sensors (Blue Trident IMU, Vicon, Oxford, UK) will be placed on the subjects' femora, thoracic and lumbar spine and on the sternum. Accelerations and angular velocity will be captured for all movement assessments.

#### **XIII. Manuel testing for muscle strength**

Selected muscles of the legs will be assessed according to Janda's M5/5 levels of strength [42]. In a sitting position: Hip flexion / M. iliopsoas (L2), Knee extension/ M. quadriceps femoris (L3). In a supine lying position: Foot extension (lift up) / M. tibialis anterior (L4), Lifting the big toe/ M. extensor hallucis longus (L5). Foot extension (push down)/ M. gastrocnemius (S1).

The test for Trendelenburg signs is done by having the patient standing on one leg. If the upper body bends spontaneously to the contralateral side the test is positive and states a weakness for the m. gluteus medius, which is primarily innervated by L5 nerve root.

#### **XIV. Physical activity level**

Physical activity (PA) level will be assessed using an activity monitor (GENEActiv, Activinsights, Kimbolton, UK) during three periods of time (9 days each). The first assessment period will take place over 9 days after the baseline measurement on test day 1. The second period will take place 6 months after the spine surgery. The third period will take place for 9 days after the follow-up study visit on test day 2. The GeneActiv activity monitor is widely used in scientific research and has been shown to be highly reliable and valid [43]. The GeneActiv will be attached to the non-dominant wrist.

#### **XV. Back performance scale**

The Back performance scale is an assessment consisting of a series of five movement activities that require mobility of the trunk. It is routinely used by physiotherapists to assess patients with back problems. The activities (sock test, pick-up test, roll-up test, fingertip-to-floor test, and lift test) all require sagittal-plane mobility and are scored from 0 (can easily do) to 3 (hard/limited to do). The test shows a good intertester agreement and test-retest reliability [44].

#### **XVI. Surgical information**

Information on the surgical procedure will be extracted from the patient files:

11. Scheduled decompression surgery
12. Scheduled fusion of vertebrae
13. Number of decompressed levels
14. Number of instrumented levels
15. In case of instrumentation:
  - Fusion with Cage
  - Fusion without Cage

#### **XVII. ICHOM**

The study cohorts will be described according to the guidelines by the International Consortium for Health Outcomes Measurements (ICHOM: [www.ichom.org](http://www.ichom.org)). The following information will be recorded for all participants:

- Age
- Sex
- Body mass
- Body height
- Body mass index (BMI)
- Pain medication
- Previous treatment (physiotherapy, infiltration, other)
- Own physical exercise program
- Duration of symptoms

### 3.4 Project plan

The project is funded by the Swiss National Foundation for a total duration of four years.

| Task                                                       | 2022 |    |    |    | 2023 |    |    |    | 2024 |    |    |    | 2025 |    |    |    | 2026 |    |
|------------------------------------------------------------|------|----|----|----|------|----|----|----|------|----|----|----|------|----|----|----|------|----|
|                                                            | Q1   | Q2 | Q3 | Q4 | Q1   | Q2 | Q3 | Q4 | Q1   | Q2 | Q3 | Q4 | Q1   | Q2 | Q3 | Q4 | Q1   | Q2 |
| Project Initiation                                         |      |    |    |    |      |    |    |    |      |    |    |    |      |    |    |    |      |    |
| Obtaining ethics approval for in vivo experimental studies |      |    |    |    |      |    |    |    |      |    |    |    |      |    |    |    |      |    |
| Baseline in vivo experimental study                        |      |    |    |    |      |    |    |    |      |    |    |    |      |    |    |    |      |    |
| Follow-up in vivo experimental study                       |      |    |    |    |      |    |    |    |      |    |    |    |      |    |    |    |      |    |
| Statistical analysis                                       |      |    |    |    |      |    |    |    |      |    |    |    |      |    |    |    |      |    |
| Output – manuscripts                                       |      |    |    |    |      |    |    |    |      |    |    |    |      |    |    |    |      |    |
| Recommendations clinical practice                          |      |    |    |    |      |    |    |    |      |    |    |    |      |    |    |    |      |    |

### 3.5 Withdrawal and discontinuation

Patients have the right to withdraw from the trial at any time for any reason and without indicating a reason. The project leader also has the right to exclude patients from the trial in the event of significant adverse events, relevant protocol deviations, administrative or other reasons. In case of withdrawal, a final assessment of the information available at withdrawal will be made. The reason for withdrawal or exclusion from the trial will be recorded. A participant needs to discontinue the project in case of withdrawal of informed consent or non-compliance. Data collected before withdrawal or discontinuation will be included in subsequent analyses to account for potential data bias.

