#### Secondary hypotheses

Hypothesis 2.1: PROMs correlate more strongly with quantitative functional parameters including muscle fatigue, spinal load and biomechanical parameters or lumbopelvic range of motion during forward trunk bending and during walking than with pathomorphological parameters including severity of stenosis, segmental instability and muscle degeneration.

Hypothesis 2.2: Changes in PROMs correlate with changes in static and dynamic spinal imbalance, muscle fatigue and extent of forward trunk bending, lumbopelvic range of motion during walking and spinal loads from before to after spinal stenosis surgery.

Hypothesis 2.3: Patients with sLSS with greater muscle degeneration and greater spinal imbalance have greater muscle fatigue.

Hypothesis 2.4: At follow-up, patients with spinal stenosis will have improved PROMs, less static and dynamic spinal imbalance and muscle fatigue, and less forward trunk bending and larger lumbopelvic range of motion during walking than before spinal stenosis surgery.

Hypothesis 2.5: Postoperative PROMs are explained by preoperative severity of LSS, spinal alignment, segmental instability, muscle degeneration, dynamic compensation, muscle fatigue and spinal load.

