## 2.3 Project design

This study is designed as a single-center, longitudinal observational study. For each patient, a multimodal set of data including experimental, clinical, functional, radiological and biomechanical data is compiled before and after routine surgical intervention. There will be two study visits: baseline and one-year follow-up (Figure 1).

[figure not shown]

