Participants will be handed out activity monitors after test-day one and test-day two. The same activity monitor will be sent to study participants six months after the spine surgery. Participants will be asked to wear the activity monitor for nine days on their wrist. Participants will be given prepaid envelopes to return the devices. In addition, participants will be asked to complete a digital set of PROMs six months after the spine surgery sent to them via e-mail. If no e-mail address is available, printed versions will be sent together with the activity monitor.

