#### **6.2 Risk-Benefit Assessment**

This project is a risk category A project. Collecting health-related personal data in this study entails minimal risks and burdens for the patient. Double sided tape will be used to attach inertial sensors and skin markers on specific anatomic landmarks. The tape may cause some skin irritation similar to a standard band-aid. Participants may experience some skin irritation at the location of skin electrodes because these locations have to be shaved and cleaned prior to electrode application. The modified Biering-Sørensen test is comparable to situations during daily, occupational or recreational activities. Overground gait analysis bears minimal risks for the patient. The MRI risk of the spine can be neglected. This standardized examination is performed in daily clinical practice. No contrast media will be given. Patients with pacemakers, neurostimulators or other incompatible devices will be excluded. All female patients prior to menopause will complete a pregnancy test before the MRI scan. If the test is positive, the patient will be excluded. EOS radiological imaging is routinely used in clinical practice. This measurement involves a minimal radiation risk (see 5.4). Measurement with Artec EVA is radiation free and fast and can lead to important conclusions about the status of the external shape and postures of patients with sLSS. This study provides no direct benefit to the patient or healthy participant. Participants will be compensated with 100 CHF for each visit. Treatment of patients with sLSS is not part of the study and will not be influenced by study participation.

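### Section 3.5 lets the project leader exclude patients on open-ended grounds and provides for no outcome collection afterwards, so loss of one-year data may be related to outcome

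*Protocol*

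**What the plan says.** Section 3.5 (Withdrawal and discontinuation) gives the project leader the right to "exclude patients from the trial in the event of significant adverse events, relevant protocol deviations, administrative or other reasons". None of these grounds is defined there. A further ground is compulsory: "A participant needs to discontinue the project in case of withdrawal of informed consent or non-compliance".

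On what happens next, the section makes two relevant commitments. First: "Data collected before withdrawal or discontinuation will be included in subsequent analyses to account for potential data bias". Second: "The reason for withdrawal or exclusion from the trial will be recorded". For withdrawal it also foresees a last assessment of whatever information is then available. It does not say whether questionnaires are sought after an exclusion.

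The rest of the design matters here:

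- Section 2.3: "There will be two study visits: baseline and one-year follow-up".
- Section 3.3: between the visits, "participants will be asked to complete a digital set of PROMs six months after the spine surgery sent to them via e-mail", with paper copies for those without an e-mail address. At the visits, questionnaires are completed on iPads, and the follow-up visit repeats the baseline procedures.
- Section 2.1, Hypothesis 2.4: "At follow-up, patients with spinal stenosis will have improved PROMs".
- Section 6.2: "Treatment of patients with sLSS is not part of the study and will not be influenced by study participation".

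**The concern.** Several secondary hypotheses depend on how patients fare after surgery. An adverse event between baseline and one year may be part of that course, yet it is a listed ground for exclusion, and the list ends in an open category. The decision may be taken by someone who knows how the patient is doing.

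Because treatment lies outside the study, excluding a patient changes only what is measured. There may be reason to stop a demanding test such as the fatigue exercise. That is no reason to stop asking the patient to fill in a questionnaire. Section 3.5 treats the two as one decision.

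At stake is whether the one-year results describe the enrolled cohort or only those who were kept. A later analysis cannot recover values that were never collected; it can only model them.

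**Working it through.** **Step 1: the plan's own attrition figure.** Section 4.1 allows 10% drop-out on 111 evaluable patients and enrols 122. Multiplying, 111 × 1.10 = 122.1, which gives the stated 122. (Dividing, 111 / 0.90 = 123.3, would give 124.) The difference does not affect this point. The 10% allowance serves below as an upper value for the share excluded.

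**Step 2: which analyses need the one-year value.**

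| Analysis | Needs one-year data? | Possible effect of outcome-related exclusion |
|---|---|---|
| H1, correlation of PROMs with dynamic compensation | Not if run on baseline data | Largely none; patients excluded later stay in |
| H2.2, correlation of changes | Yes | Selection or range restriction, sign unknown |
| H2.4, improvement at follow-up (paired t-tests, section 4.2) | Yes | Improvement may be overstated |
| H2.5, explaining postoperative PROMs | Yes, where the outcome is the one-year PROM | Selection or range restriction, sign unknown |

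A patient excluded before the one-year visit has no pre-post difference to that visit. That patient drops out of the paired tests and change correlations unless the value is imputed. Section 4.3 says only that multiple imputation will be considered if missingness is unexpected.

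**Step 3: size of the possible bias for H2.4.** Let q be the share excluded, M_R the mean improvement of retained patients and M_E that of excluded patients, with D = M_R − M_E.

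- Full-cohort mean = (1 − q) × M_R + q × M_E
- Overstatement = M_R − full-cohort mean = q × D

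The documents give neither q nor D, so both are assumptions. Results in ODI points:

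| q | D = 10 | D = 15 | D = 20 |
|---|---|---|---|
| 3% | 0.30 | 0.45 | 0.60 |
| 5% | 0.50 | 0.75 | 1.00 |
| 10% | 1.00 | 1.50 | 2.00 |

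Of 122 patients, 3% is about 4 (0.03 × 122 = 3.7) and 10% is about 12 (0.10 × 122 = 12.2). In standard deviations of change, with D from 0.5 to 2 SD, the overstatement is 0.025-0.10 SD at q = 5% and 0.05-0.20 SD at q = 10%. If D = 0, as might be so for purely administrative exclusions, it is zero at any q.

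D is measured here against the retained patients. Measured against the full-cohort mean, the factor becomes q / (1 − q), and the top of the range is 0.10 / 0.90 × 20 = 2.2 points.

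**The case against.** The strongest reply is that section 3.5 grants a permission and predicts nothing about its use. This stands. A reader might infer that the rule stops follow-up in patients who do badly and so makes the one-year results look better. The documents do not support that. Significant adverse events are not defined in section 3.5. The only event definition, in section 5.3, concerns serious events possibly attributable to sampling or data collection, so surgical complications are neither named nor ruled out. Exclusions for protocol deviations, administrative or other reasons have no known direction.

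A reader might also infer that the study's main result is at risk. It is not clearly so: the primary hypothesis is a correlation, and only secondary hypotheses plainly need follow-up data.

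The protocol does have mitigation. Reasons are recorded, earlier data are kept, and six-month PROMs from patients excluded later would be useful auxiliary information if imputation were used. This lessens the problem, but imputation from earlier values still rests on assumptions that cannot be checked when the reason for exclusion is itself linked to the course.

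Finally, sensitivity analyses and reporting detail may be in an analysis plan not seen here. That is fair for the analysis. It does not answer a protocol rule that lets outcome collection end.

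**Conclusion.** The point holds as a weakness in a stated rule. Section 3.5 permits discretionary, possibly outcome-related exclusion after baseline without providing for outcomes to be sought afterwards, and the safeguard it names does not supply the missing one-year value.

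The likely size is modest: an overstatement of about 0.3-2.0 ODI points in the pre-post improvement under the assumptions above. The upper end spends the whole 10% drop-out allowance on patients who improve 20 points less. Nothing here shows that a conclusion on Hypothesis 2.4 would change. For Hypotheses 2.2 and 2.5 no direction can be given. This is a cheap improvement, worth making because data not collected cannot be regained.

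**What to change.** In section 3.5:

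1. Separate two decisions: stopping laboratory or imaging assessments, and leaving follow-up. State that the first does not imply the second, and word the non-compliance sentence to match.
2. Seek the six-month and one-year PROMs from every patient who has not withdrawn consent. Section 3.3 describes remote collection only at six months, so extend that e-mail or paper route to one year for patients who do not attend the visit.
3. Remove or narrow the administrative and other reasons as grounds for ending outcome collection.
4. Report exclusions by the reason that is already to be recorded.

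The cost is a few sentences in section 3.5, a matching addition to section 3.3, and a small number of extra remote questionnaires. Some patients will have one-year PROMs without one-year biomechanics; they can enter the PROM comparison but not the analyses that need both. Clinical care is not touched.

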## 4 STATISTICS AND METHODOLOGY

### 4.1 Sample size calculation

To determine if PROMs correlate with dynamic compensation considering categorical covariates with 3 levels of the covariate a sample size of 111 (37 within each level) is required to detect a correlation of 0.3 at 80% power and 5% significance level. Considering a 10% drop-out rate, 122 subjects will be enrolled in the study.

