#### Primary hypothesis

Hypothesis 1: PROMs correlate with dynamic compensation (difference between static and dynamic sagittal spinal alignment) in patients with sLSS.

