### 4.2. Statistical analysis plan

Baseline variables will be reported using mean and standard deviation, or median and interquartile range for continuous variables, and as counts and percentages for the categorical variables. Correlation analysis will be used for analysing the association between PROMs and continuous variables, including dynamic compensation, spinal imbalance, segmental instability, muscle degeneration and fatigue, and biomechanical parameters. For measuring the association between categorical variables (e.g., the severity of stenosis) and PROMs, we will perform an analysis of variance (ANOVA). Pre- to postoperative differences in PROMs, dynamic compensation, the severity of stenosis, spinal alignment, segmental instability, muscle degeneration, muscle fatigue, and biomechanical parameters will be assessed by comparing means using paired t-tests for continuous variables, and by comparing frequencies using the chi-square test for the categorical variables. Associations of pre- to postoperative changes in PROMs with changes in static and dynamic spinal imbalance, muscle fatigue, and extent of forwarding trunk bending and lumbopelvic range of motion during walking from before to after spinal stenosis operation will be assessed by computing the difference for each variable from before and after surgery for each patient and evaluating the correlation between these computed differences. The statistical methods described here assume the normal distribution of all parameters. In case of

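### Section 4.1 gives 111 patients as the number needed to detect a correlation of 0.3, but that test needs 85 (87 if adjusted for a 3-level covariate), and the calculation does not match the plain correlation planned in section 4.2

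*Protocol*

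**What the plan says.** The primary hypothesis (section 2.1) is that "PROMs correlate with dynamic compensation (difference between static and dynamic sagittal spinal alignment) in patients with sLSS". Section 4.1 sizes the study for it, "considering categorical covariates with 3 levels of the covariate", and concludes that "a sample size of 111 (37 within each level) is required to detect a correlation of 0.3 at 80% power and 5% significance level". It continues: "Considering a 10% drop-out rate, 122 subjects will be enrolled in the study". It does not name the covariate, the test, the formula or the sidedness.

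Section 4.2 states the matching analysis: "Correlation analysis will be used for analysing the association between PROMs and continuous variables", with dynamic compensation among those variables. It mentions no adjustment or stratification for this analysis. Categorical variables, with stenosis severity as the example, are related to PROMs in a separate ANOVA.

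**The concern.** Two things do not fit. First, 111 is more than a correlation of 0.3 needs at 80% power and 5% significance, so a reader who checks the sentence that justifies the study's size will not recover its figure. Second, the calculation allows for a 3-level covariate, while the analysis in section 4.2 has none, so the study is sized for one analysis and plans another.

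At stake is whether the sample-size justification is correct and can be traced to the primary analysis. It would be carried into publications, where a wrong effect measure or an unexplained covariate would be open to challenge.

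**Working it through.** **Inputs.** From section 4.1: r = 0.3, power 80%, significance level 5%, one covariate with 3 levels, 111 evaluable (3 × 37), 10% drop-out, 122 enrolled. Sidedness is not stated; two-sided is assumed, and one-sided is also shown.

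**Step 1. Can 111 be reproduced as a correlation test?** Fisher's z gives n = ((z_α + z_power) / atanh(r))² + 3, with atanh(0.3) = 0.3095.

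- Two-sided: ((1.960 + 0.842) / 0.3095)² + 3 = 84.9, so **85**.
- One-sided: 67.5, so 68.
- Partial correlation, two dummy variables for the 3-level covariate: 84.9 + 2 = 86.9, so **87**.
- Fisher's z pooled within three strata (3 lost per stratum, not 3 in all): 84.9 − 3 + 9 = 90.9, so 91.
- Spearman, which the nonparametric fallback in section 4.2 would allow: 89 to 90, depending on the variance formula.

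None gives 111. Raising power to 90% (112.7) or lowering α to 0.05/3 (112.3) gives 113. Neither is what section 4.1 states, and neither is 111.

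**Step 2. What does give 111 with 37 per level?** Take a one-way ANOVA F test with 3 groups and Cohen's f = 0.3, for which the noncentrality is f² × N.

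| Patients per group | Total N | f² × N | df | Power at 5% |
|---|---|---|---|---|
| 36 | 108 | 9.72 | 2, 105 | 79.2% |
| 37 | 111 | 9.99 | 2, 108 | 80.3% |

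So 37 per group is the smallest equal group size that reaches 80%. Adding one continuous covariate (ANCOVA) leaves 80.3% at 111. The match is exact in both the total and the group size. It suggests that 0.3 is an f for differences between group means, labelled as a correlation. This origin is inferred from the numbers; the protocol does not state it.

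**Step 3. Power of the planned correlation at r = 0.3.** Power = Φ(0.3095 × √(n − 3 − k) − 1.960), with k = 0 unadjusted and k = 2 adjusted. For example, at n = 111 unadjusted: Φ(0.3095 × √108 − 1.960) = 0.896.

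| n | How it arises | Unadjusted | Adjusted |
|---|---|---|---|
| 85 | smallest n for 80%, unadjusted | 80.0% | 79.1% |
| 109 | 122 × 0.9 = 109.8, rounded down | 89.0% | 88.4% |
| 111 | stated in section 4.1 | 89.6% | 89.0% |
| 122 | no loss | 92.2% | 91.7% |

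Simulation (50,000 runs) of the unadjusted test gave 80.7% at 85 and 89.7% at 111, in agreement.

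**The case against.** The best defence is that the error is on the safe side. The planned overall correlation has 89 to 90% power at 109 to 111 patients against the 80% claimed, so enrolment need not change. This stands, and it limits the severity. It does not make the stated requirement true, nor does it bring sections 4.1 and 4.2 into line.

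A second defence is that covariates and model terms are commonly left to a statistical analysis plan, which is not shown. That is fair as to which covariate is meant. But the protocol itself contains both the covariate-based sizing and the analysis without a covariate, and the two disagree as written.

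Three stronger readings are tempting, and the protocol does not support them:

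- *That 111 cannot be derived at all.* It can, as a 3-group F test with f = 0.3. The fault is the test and the effect measure, not an arbitrary number.
- *That the study is underpowered because 37 patients give only about 44% power for r = 0.3.* That figure assumes a separate correlation test in each level. Neither section plans one; the 37 reads naturally as 111 split evenly over three groups.
- *That the drop-out step leaves the study short.* Dividing gives 111 / 0.9 = 123.3, so 124, where 111 × 1.1 = 122.1 gave 122. Two patients have no consequence when 85 to 87 suffice.

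**Conclusion.** The concern holds as a correction of moderate severity. For the stated correlation, power and significance level, the requirement is 85 patients (87 adjusted), not 111; section 4.1 overstates it by 26 (24 adjusted). The covariate behind the calculation is unnamed and does not enter the primary correlation in section 4.2.

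The primary analysis is adequately powered at r = 0.3: about 89% with 109 evaluable patients (88% adjusted). The primary hypothesis names no time point. If it is tested on baseline data, one-year loss would not reduce the sample, and power could approach the 92% shown for 122.

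The power figures assume a two-sided 5% test, a true correlation of 0.3 and approximate normality. The ANOVA explanation is an inference; the failure to reproduce 111 as a correlation does not depend on it.

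**What to change.** Keep 122 enrolled and restate section 4.1 for the analysis that section 4.2 plans. Suggested wording:

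> For the correlation of PROMs with dynamic compensation, 85 evaluable patients give 80% power to detect r = 0.3 at a two-sided 5% level. Enrolling 122 leaves about 109 after 10% loss, giving about 89% power.

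Delete the reference to a 3-level covariate and to 37 patients per level.

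If a covariate-adjusted analysis is intended instead, name the covariate in section 4.1, give 87 patients for 80% power and about 88% power at 109, and state the same adjusted analysis in section 4.2. That choice is for the authors; either route makes the two sections agree.

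If the figure did come from a 3-group ANOVA, it should not be described as a correlation.

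The cost is a change of protocol wording. Recruitment and procedures are unaffected, and no extra patients are needed.

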### **3. PROJECT POPULATION AND STUDY PROCEDURES**

#### **3.1 Project population, inclusion and exclusion criteria**

We plan to include 122 patients with sLSS (61 per year) in this study, which will be realistic and sufficient for the proposed statistical analysis (see Section 4.1). Patients will be recruited at the Department of Spine Surgery at the University Hospital Basel. The surgical procedure is not affected by the study and is not subject of investigation. All patients will receive – depending on their clinical and imaging diagnostics – lumbar decompression alone or decompression combined with fusion either through posterolateral fusion with pedicle screw-rod system with autologous bone apposition or through transforaminal lumbar interbody fusion with a cage filled with autologous bone implanted from posterolateral into the intervertebral space. Decompression will be performed as either open surgery or microsurgical technique, and both are performed through a midline approach. The open surgery decompression will be performed via an interspinous approach with interlaminar flavectomy, whereas in the microsurgical technique, uni- or bilateral fenestration and flavectomy will be performed.

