#### **4.3. Handling of missing data**

All data will be checked for quality and completeness at the time of testing. Hence, we do not expect missing data due to technical difficulties. A 10% drop-out rate was considered in the sample size calculation (section 4.1), however, in case of an unexpected missingness after assessment of the reason for missingness in the variables we will consider using multiple imputation techniques to impute the missing information.

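### At the protocol's own 10% drop-out rate, enrolling 122 leaves about 110 patients, slightly under the 111 that Section 4.1 requires

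*Protocol*

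**What the plan says.** Section 4.1 sizes the study on the correlation between PROMs and dynamic compensation, which is Hypothesis 1. It allows for a three-level categorical covariate and states that "a sample size of 111 (37 within each level) is required to detect a correlation of 0.3 at 80% power and 5% significance level". The enrolment target follows directly: "Considering a 10% drop-out rate, 122 subjects will be enrolled in the study".

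Two other sections lean on this step. Section 3.1 repeats the target, "We plan to include 122 patients with sLSS (61 per year) in this study", and calls it sufficient for the planned analysis, pointing to 4.1. Section 4.3 refers back to it when it deals with missing data: "A 10% drop-out rate was considered in the sample size calculation (section 4.1"), and adds multiple imputation as an option for missingness that was not expected.

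Hypothesis 1 (Section 2.1) and the primary endpoints (Section 2.2) name no visit. Section 2.3 plans one visit before surgery and one a year later, and Section 3.3 says that the two visits use the same procedures. ODI and dynamic compensation are therefore collected twice.

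**The concern.** The protocol presents 111 as a requirement and 122 as the number that secures it against 10% loss. Applied to 122, that rate leaves fewer than 111. The sentence that justifies enrolment thus does not deliver what it states, and the figure is carried into 3.1 and 4.3 and would probably be carried into publications.

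A second point is tied to the first. Whether the loss matters for the hypothesis that was sized depends on when that hypothesis is tested, and the protocol does not say. At stake are the accuracy of the sample-size statement and a clear account of which analyses the drop-out reaches. The viability of the study is not in question.

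**Working it through.** **Inputs.** Required number N = 111 = 3 × 37; drop-out d = 0.10; enrolled 122; r = 0.3; power 80%; significance level 5% (all Section 4.1; 122 also in 3.1, 10% also in 4.3). Sidedness is not stated; two-sided is assumed below.

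**1. Reproducing 122.** N × (1 + d) = 111 × 1.10 = 122.1, truncated to 122.

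**2. What 122 leaves.** 122 × (1 − 0.10) = 109.8, so 109 or 110 whole patients, 1 to 2 below 111. Per level, 109.8 / 3 = 36.6 against 37.

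**3. The number that meets the stated aim.** N / (1 − d) = 111 / 0.90 = 123.3, so 124. Check: 124 × 0.90 = 111.6, while 123 × 0.90 = 110.7 is still short. The gap in enrolment is 124 − 122 = 2 patients (2/124 = 1.6%).

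**4. Drop-out that 122 can absorb.** 1 − 111/122 = 11/122 = 9.0%.

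**5. Cost in power.** Fisher z, two-sided 5%, true r = 0.3. Simple correlation: power = Φ(atanh(0.3) × √(n − 3) − 1.960). Pooled over three strata: the same with √(n − 9). Smallest simple correlation detectable at 80% power: tanh((1.960 + 0.842) / √(n − 3)).

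| n | Power, simple | Power, three strata | Detectable r |
|---|---|---|---|
| 109 | 89.0% | 87.2% | 0.266 |
| 110 | 89.3% | 87.5% | 0.264 |
| 111 | 89.6% | 87.8% | 0.263 |
| 122 | 92.2% | 90.8% | 0.251 |

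Going from 111 to 109 costs 0.6 points in either column and moves the detectable correlation by 0.003.

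These formulas do not reproduce 111. For 80% power they ask for 85 (simple), 87 (adjusting for two dummy variables) or 93 (3 × 31, pooled over strata). The protocol gives no formula, so only the differences between rows should be relied on, not the power levels. As a further check, an F test with R² = 0.09 and one to five coefficients loses between 0.5 points (90.7% to 90.2%) and 0.97 points (69.8% to 68.9%) from 111 to 109. The loss stays under one point throughout.

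**6. Which analysis the loss reaches.** Dynamic compensation contrasts standing with walking alignment within one session, so one visit yields a complete pair for Hypothesis 1.
- If Hypothesis 1 uses baseline data, loss after that visit removes nobody from it. Up to 122 are available against 111.
- If Hypothesis 1 needs one-year data, or if patients are lost before their baseline assessments are complete, the 10% applies and about 110 remain against 111.

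**The case against.** The strongest reply is that this is a rounding-scale slip. Two more enrolled patients would close it, power barely moves, and on the simple Fisher formula 109 pairs still detect correlations smaller than the planned 0.3. That stands, and it sets the weight of the point. It does not make the sentence in 4.1 correct.

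A reader might infer more, and the protocol does not support it:

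- *That the allowance is misplaced because Hypothesis 1 is measured only at baseline.* Baseline is a plausible reading, but no section fixes it and both endpoints are collected at both visits. Some loss before a usable pair is also possible, since consent is signed on arrival, before the questionnaires and motion capture (Section 3.3), and Section 3.5 allows the project leader to exclude patients.
- *That the study both falls short for Hypothesis 1 and attaches drop-out to the wrong hypothesis.* These cannot both hold. If Hypothesis 1 uses baseline only, follow-up loss causes no shortfall against 111. If the loss does reach Hypothesis 1, the allowance is where it belongs.
- *That Section 4.3 assures readers that the one-year analyses are covered.* It says only that a 10% rate was taken into account in 4.1. It claims no power for the one-year hypotheses, and Section 3.5 keeps data collected before withdrawal.
- *That 4.1 should have sized Hypotheses 2.2, 2.4 and 2.5.* These are secondary, and sizing a study on its primary hypothesis alone is ordinary practice.

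**Conclusion.** The inflation step in Section 4.1 is wrong by its own terms: 122 enrolled at 10% drop-out leaves about 110 (109.8), not 111, and secures 111 only up to 9.0% loss. The size is 1 to 2 patients and under one percentage point of power, so this is a minor correction.

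The arithmetic rests only on the protocol's 111, 122 and 10%, and holds however 111 was derived. The power figures assume a two-sided test and the formulas shown. Whether Hypothesis 1 itself is affected cannot be decided from the protocol, because its visit is not named. Naming the visit is the other half of the correction.

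**What to change.** Leave enrolment at 122 and correct the wording.

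1. In Section 4.1, replace the drop-out sentence with, for example: *With 122 enrolled, about 110 remain at 10% drop-out; 111 remain if drop-out is at most 9%.* Bring the matching statements in 3.1 and 4.3 into line.
2. State which visit Hypothesis 1 uses. If it is baseline, add: *All patients with complete baseline data contribute to Hypothesis 1; the 10% loss applies to the one-year analyses (Hypotheses 2.2, 2.4 and 2.5).*

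The cost is a few sentences in three sections, with no change to procedures or patient burden. The stated figure becomes slightly less favourable. Keeping both 111 and 10% as firm requirements would instead mean enrolling 124, but the effect on power does not call for that.
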